### Adverse event reporting

The research team will record adverse events related to each participant from the time of enrollment to the last follow-up assessment visit, which include: 1) unintentional loss of balance (i.e., fall to the ground); 2) change in systolic pressure to >140 mm Hg and/or diastolic pressure exceeding >90 mm Hg^46,60^; 3) AD with SBP >150 or >20 mm Hg from baseline with complaints of headache, diaphoresis, and/or blurred vision; 4) musculoskeletal injury during/after walking training (i.e., sprain, fracture, etc.); 5) symptoms such as pain, soreness, numbness, or signs of injury (inflammation, blisters, etc.) during or immediately after training or on returning home; 6) hospitalization for any cause; and 7) death attributable to any cause. Serious and/or unexpected adverse events will be immediately reported to the MGB IRB.

### Study compensation

Participants receive $40 per visit and up to $300 in travel reimbursement.

### Study limitations

Clinical trials are necessary for the study of combinatorial interventions to treat SCI. However, the experimental protocols for these trials are often beset with study design challenges attributable, in part, to confounding treatment interactions, small sample size, short study duration, and SCI heterogeneity. The study of multiple treatments and their interactions requires the appropriate choice of controls to discriminate between the clinical outcome of the treatments alone, combined, or neither. Identifying the study groups is pivotal to trial success, but requires larger sample sizes. Because of challenges from the ethical perspective in SCI research with humans, we cannot include a control (no treatment) group in the present trial. We anticipate that some participants will receive additional therapy services upon study enrollment.

We will quantify the interactions between frequency/duration of these services and our primary outcome measures. The biostatistician also will use multi-variate statistical models to assess these and other potential confounds to our outcome measures. Though most studies continue for longer periods (e.g., 12 weeks),^61^ up to eight sessions of tAIH or WALK_tSTIM_ are sufficient to elicit improvements in walking speed in persons with SCI.^6,8,62^ To consider the potential long-term effects of tAIH + WALK_tSTIM_ on walking ability, we will follow up at 1, 4, and 8 weeks post-treatment.

Small sample sizes can undermine the translation of results to the larger heterogeneous patient population. We also acknowledge that balancing treatment groups of a heterogeneous SCI cohort will be a challenge. To address this obstacle, we will consider age, sex, reliance on walking aids,^63^ and injury level. Second, we do not yet know the potency of WALK_tSTIM_ and eight sessions may be considered too few to achieve MCID in the treatment groups. We chose eight sessions to remain pragmatic in treatment duration while aligning our study design to a recent placebo-controlled trial that found WALK_tSTIM_ induced clinically significant gains in walking speed within six sessions.^62^ We acknowledge that achieving MCID in eight sessions may not occur during treatments without tAIH. If this happens, we will compare groups using survival-type analyses to include those with no participants who achieved MCID.^64^ Third, medication changes are frequent in persons with SCI, which may alter neural plasticity.

While our proposed study will allow for changes in pharmacological regimens only after (not during) our intervention sessions, we will monitor medication dosing throughout the study and account for them as covariate factors in our statistical models. The statistical power computed from our preliminary data involving a heterogeneous cohort of SCI persons offers confidence that our estimated sample size will detect differences between interventions if they exist.

Several concomitant factors can weaken the interpretation of the study results. Concomitant medication used (e.g., for bowel/bladder dysfunction, systemic hypertension, pain, spasticity, and depressive symptoms) may confound the effects of tAIH intervention. The stability of the medication regimen prior to enrollment may limit confounding effects. Future clinical integration of this combinatorial treatment is possible based on the simplicity, low-cost, and non-invasiveness of administering tAIH and tSTIM. We anticipate that results from this trial will provide new understandings of combinatorial treatments to augment traditional physical therapy.

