### Randomization

Before enrolling the first study participant, a research statistician generated the balanced randomization scheme for treatment allocation at both clinical sites using the R Statistical Package.^21^ This method randomly assigns participants to one of three intervention groups (*N* = 20 per group): 1) tAIH + WALK_tSTIM_, 2) tAIH + WALK_tSHAM_, and 3) Placebo + WALK_tSTIM_ in blocks of 6 participants. Using this scheme, the site coordinator will assign each participant to their respective intervention group in the order in which they complete the walking practice sessions. Although the coordinator informs participants about their possible group assignment, they will be blinded to the treatment they receive (i.e., tAIH or Placebo, WALK_tSTIM_, or WALK_tSHAM_). The clinical raters and trainers will also be unaware of each participant's treatment assignment. Based upon reports from participants blinded during our previous tAIH study,^6^ >75% guessed incorrectly or were uncertain of the breathing intervention received, suggesting that our previous blinding and air delivery methods were effective.

We plan a similar integrity analysis for the stimulation sham protocols (no stimulation). Participants guess the interventions received at the end of each treatment session and indicate their guess confidence using a Likert scale.^22,23^ Using a contingency table and Fisher's exact test, we will determine whether the probability of correct guessing differs from chance.

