#### Concomitant medication

Medication use (e.g., bowel/bladder dysfunction, systemic hypertension, pain, spasticity, and antidepressant medications) is common after SCI and may confound the effects of our interventions. Because of participant safety and comfort, we will not limit prescribed medication use. We will require those receiving medication to maintain the dose 1 week before and during the intervention sessions, as we did in our previous study.^6,8^ The team physicians work with the study participant to ensure that medication dosing is stable before enrollment and during interventions. We log any change in medication for each participant throughout the study and assess for possible drug-tAIH interactions and changes in prescribed drug dosages at follow-ups. If participants must change their medications for safety, they can readily withdraw from the study at any time.

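### Medication changes made after allocation are to enter the models as covariates, which can bias the group comparisons at the 1-, 4- and 8-week follow-ups

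*Protocol article*

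**What the plan says.** **Medication.** Study limitations in the protocol article says the trial will "allow for changes in pharmacological regimens only after (not during) our intervention sessions", and then that dosing is monitored for the whole study and that the team will "account for them as covariate factors in our statistical models". The Concomitant medication section requires stable doses from one week before and through the intervention sessions. It adds "We log any change in medication for each participant throughout the study", with assessment of "changes in prescribed drug dosages at follow-ups". Table 2 collects medication at screening, baseline, testing and follow-up visits.

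**Allocation.** Under Randomization, "the site coordinator will assign each participant to their respective intervention group in the order in which they complete the walking practice sessions". The eight combination sessions come after that.

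**Models.** Under Hypothesis 1 the main mixed model has intervention and time as fixed effects and subject as random effect. A further mixed model controls for study period, baseline values of the primary outcomes, and demographics. The Hypothesis 2 model has treatment group and baseline 10MWT speed. None of them names medication.

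**Additional therapy.** Study limitations says "We anticipate that some participants will receive additional therapy services upon study enrollment" and "We will quantify the interactions between frequency/duration of these services and our primary outcome measures". Multivariate models are then to assess these services and other possible confounds.

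**The concern.** Randomisation makes the groups comparable on everything fixed before allocation. A covariate measured later keeps that comparability only if neither treatment nor the response to it can change the covariate. A participant whose spasticity or pain falls may have the drug for it reduced, and one whose blood pressure rises may have a drug added. Medication change is then partly a result of treatment. Conditioning on it either removes the part of the effect that runs through medication, or links treatment to unmeasured causes of both medication use and walking.

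At stake is the persistence part of Aim 1. The hypothesis concerns enduring gains, and the 1-, 4- and 8-week visits that test it fall in the period when regimens may change. An adjusted estimate at those visits would no longer be the plain comparison of randomised groups.

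**Working it through.** **1. Order of events.** Walking practice (8 sessions), then allocation, then 8 combination sessions under stable dosing (T1, T2), then follow-up at 1, 4 and 8 weeks with changes allowed. By the plan's own rule, every permitted change lies after allocation and after T2.

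**2. Could treatment affect medication?** The outcome sections and Hypothesis 3 follow pain, spasticity, hypertension and autonomic dysreflexia as possible consequences of the interventions. Concomitant medication names drugs for pain, spasticity and hypertension. The link is plausible on the article's own account, but it is not quantified.

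**3. Which model?** Study limitations speaks of the statistical models without naming one. The Hypothesis 1 and 2 sections list covariates and leave medication out. The two places do not give the same adjustment set.

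**4. Scale for the illustrations.** The Sample size section gives a difference of −3.14 s (combination versus tAIH with sham stimulation), SDs of 3.0 and 2.0 s, 16 completers per group and alpha 0.0167 (two-sided assumed). SE = √((9 + 4)/16) = 0.901 and 3.14/0.901 = 3.48. With 30 df the noncentral t gives power 82.2% (Welch 81.5%), in line with the stated figure of more than 81%. These inputs serve only as a scale; no power correction follows from this point.

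**5. Linear illustration (all link values assumed).** Let T be treatment, M a post-allocation medication measure with within-group SD 1, and U an unmeasured cause of both M and walking:

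- M = aT + cU + error
- Y = (−3.14 − ab)T + bM + gU + error, so the total effect is −3.14 s

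Adjusting for M gives a treatment coefficient of −3.14 − a(b + cg), so the bias is −a(b + cg). Regressions on 400,000 simulated participants agree to within 0.02 s.

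| a | b | c | g | Adjusted effect (s) | Change relative to 3.14 s |
|---|---|---|---|---|---|
| 0 | any | any | any | −3.14 | none |
| −0.25 | −1 | 0.5 | 1.5 | −3.20 | 2% larger |
| −0.5 | −1 | 0 | 0 | −3.64 | 16% larger |
| −0.5 | 0 | 0.5 | 1.5 | −2.77 | 12% smaller |
| −1.0 | −1 | 0 | 0 | −4.14 | 32% larger |
| −1.0 | 0 | 0.5 | 1.5 | −2.39 | 24% smaller |

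**6. Illustration with a yes/no medication reduction (assumed).** Outcome y = −3.14T + 2.55e with e standard normal and 2.55 = √((9 + 4)/2). P(reduction) = expit(k − s·y), so a larger improvement makes a reduction more likely. The adjusted effect is the coefficient of T in a regression of y on T and the indicator.

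| k | s | Reduction, combination vs comparator | Adjusted effect (s) | Attenuation |
|---|---|---|---|---|
| −1 | 0 | equal | −3.14 | none |
| −1 | 0.1 | 34% vs 27% | −3.10 | about 1% |
| −3 | 0.3 | about 13% vs 6% | −3.00 | about 4% |
| −1 | 0.3 | 49% vs 29% | −2.80 | 11% |
| −1 | 0.5 | 61% vs 32% | −2.41 | 23% |

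The last two rows need very frequent reductions that differ widely between arms. The documents give no rates against which to judge any row.

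**The case against.** The strongest reply has four parts.

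- *The sentence sits among the limitations and names no model.* The hypothesis-testing models do not list medication, so the sentence could refer to supplementary models. A reader might infer that the primary efficacy model will contain it; the article does not say so. What remains is that it is the article's only statement of how medication enters the models, it is worded as a commitment, and nothing restricts it to baseline values or sensitivity work.
- *Stable dosing protects much of the trial.* This stands. T1, T2 and the number of sessions to reach the MCID are observed while doses are meant to be constant. A reader might infer that all efficacy results are affected; the article's own rule limits the exposure to follow-up.
- *Additional therapy is handled differently.* This also stands. A reader might take it as a second commitment to adjust. The article says only that these services will be quantified against the outcomes and assessed as possible confounds, and some begin at enrolment, before allocation. Use after allocation would raise the same problem if it were put into the efficacy models.
- *The size is assumed.* This stands too. An attenuation of 11% to 23% might be read as the expected bias, but it depends on change rates the documents do not give. Milder links give 1% to 4%, and other structures reverse the sign.

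**Conclusion.** The point holds for medication and for the follow-up visits. As written, the plan allows covariates that arise after randomisation, and that treatment may influence, into models that compare the groups at 1, 4 and 8 weeks. It also leaves two different adjustment sets in the same article.

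The bias is conditional. There is none if neither treatment nor response affects medication. Under the assumed links above it runs from about 1% to over 20% of a 3.14 s effect, towards or away from no difference. Since the sign cannot be known beforehand, the adjustment cannot be defended as conservative. The protection of T1 and T2 assumes that stable dosing is kept and that medication is entered as its value at each visit; the article does not give the coding.

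This should be corrected before analysis. It does not undermine the design.

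**What to change.** Replace the sentence in Study limitations, and align it with the Hypothesis 1 and 2 sections, so that:

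1. covariates in the efficacy models are limited to values fixed before allocation, such as the outcome at T0, site, and medication class at T0;
2. medication changes after allocation are summarised by arm and visit;
3. any analysis that adjusts for those changes is labelled as a sensitivity analysis, with its handling of them as intercurrent events stated;
4. only therapy use before allocation may enter the efficacy models, and later use is reported descriptively or in a sensitivity analysis.

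The cost is analysis wording only. Medication is already recorded at every visit, so the medication part needs no new data, and neither the sample size nor the schedule changes.

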## Discussion

This study aims to examine the efficacy, potency, and persistency of daily tAIH priming to boost the training-related effects of WALK_tSTIM_ on walking recovery in persons with chronic SCI. Prior studies show that daily tAIH elicits rapid improvements in overground walking ability when used alone or as a combinatorial approach, compared to training alone.^6–8,65^ Indeed, restoring community walking is a top priority for persons living with SCI, as improvements in walking function enable them to participate more independently in a broad range of daily living activities and combat the deleterious effects of secondary health conditions. Traditional gait training approaches offer only modest recovery of walking function in persons with SCI.^66^ Thus, treatments that may trigger mechanisms of neural plasticity within spared spinal pathways in a safe and efficacious manner, regardless of ambulatory status, is a top priority in SCI medicine.^67,68^ Follow-ups with participants months after the intervention ends will allow us to analyze the longevity of walking recovery. We anticipate that outcomes from this study will provide new insights into the potential clinical utility of tAIH-based translational approaches to boost training-related gains in functional mobility after SCI.

## Data Availability

Final trial data are accessible to the study investigators. However, individual data requests should be made to the principal investigator. The research team plans to disseminate results through published manuscripts and presentations. We also plan to make information available through the Spinal Cord Injury Common Data Elements (CDE) standards developed through the collaboration of the International Spinal Cord Society, the American Spinal Injury Association, and the National Institutes of Health National Institute of Neurological Disorders and Stroke. Per request of the funding agency's Program Office, we will submit data for USAMRMC archiving in accordance with privacy policies of the USAMRMC and institutional review boards at the collaborating sites: Spaulding Rehabilitation Hospital and Shirley Ryan AbilityLab.

## Abbreviations Used

6MWT: 6-Minute Walk Test
10MWT: 10-Meter Walk Test
AD: autonomic dysreflexia
AIS: American Spinal Injury Association Impairment Scale
ANOVA: analysis of variance
BDNF: brain-derived neurotrophic factor
BP: blood pressure
HR: heart rate
IRB: institutional review board
LEMS: lower extremity motor score
MCID: minimal clinically important difference
MGB: Mass General Brigham
MMSE: Mini-Mental State Examination
NBSS: Neurogenic Bladder Symptom Score
NBDS: Neurogenic Bowel Dysfunction Score
NPRS: Numeric Pain Rating Scale
O-TMT: Oral Trail Making Test
SBP: systolic BP
SCATS: SCI Assessment Tool for Spastic Reflexes
SCI: spinal cord injury
SCI-FAI: SCI Functional Ambulation Inventory
SpO_2_: peripheral blood oxygen saturation
tAIH: therapeutic acute intermittent hypoxia
tSTIM: transcutaneous spinal stimulation
TUG: Timed Up and Go Test
WALK: walking practice
WALK_tSHAM_: WALK and transcutaneous sham stimulation
WALK_tSTIM_: transcutaneous spinal stimulation-enhanced walking therapy
WISCI: Walking Index for Spinal Cord Injury
